**Methods/design:**

In a randomised, controlled interventional superiority-trial, individuals older than 65 years of age living in the community or nursing homes will be randomised into two groups. The study will be conducted in two study centres with assessments at baseline, 6 and 12 months. The intervention group will participate in a supported physical activity intervention for 6 months. An assigned volunteer will visit them three times a week for an outdoor walk between 30 and 50 min, or equivalent indoor activity. Persons in the control group will be invited to two lectures covering topics related to health. Primary endpoint is the physical function measured by the Short Physical Performance Battery (SPPB) at baseline, after 6 and 12 months. Secondary and safety endpoints will be quality of life (EQ. 5D), fear of falling (Falls Efficacy Scale), physical activity (activity diary), cognitive executive function (clock drawing test), falls requiring medical attention, hospitalisation and death. Primary analysis will be carried out by intention to treat.

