### Statistical analysis

#### Sample size

Sample size calculation was carried out based on expected effects regarding the primary outcome (physical function measured by the Short Physical Performance Battery [13] after 6 months of intervention (T1). A change of 1 point has been shown to be clinically relevant (e.g. predictive of future hospitalisation, health improvement and mortality) [33]. The standard deviation in comparable samples has ranged between 2.6 and 2.8 points [30, 31]. With a conservative approach, we assumed the higher standard deviation (2.8) for our calculation. In an analysis of covariance (including baseline values of the primary outcome), with an R-square of 0.5 for the covariate and a power of 95% (1-β), sample sizes of *n*=103 will be required for each of the two groups. The total sample of 206 participants achieves 95% power to detect differences among the means using an F test with a 5% significance level. The size of the variation in the means is represented by their standard deviation, which is 0.50. The common standard deviation within a group is assumed to be 2.8.

In our pilot study [12] conducted in nursing homes, we experienced a loss of 28% during the 6 months intervention period mainly due to death and hospitalisation. From our experience, the loss of participants recruited in primary care practices will be lower. A British primary care and community based study, which examined a complex nurse-delivered intervention with self-paced exercises and therefore people who are likely to be physically healthier (compared to our participants), experienced a loss of 6% during 3 months [9]. Considering that we are now also recruiting participants in community settings (living at home, primary care) and following a conservative approach, we set the expected loss during the intervention period to 40% (mainly due to death and hospitalisation). Assuming a loss of 40% during the 6 months of intervention we will need a total sample of *n*=345 to achieve adequate power of 95% at our primary endpoint. This will also enable us to achieve enough power for the analyses of secondary endpoints. The study centre Marburg will aim to recruit 230 persons from the community setting and the study centre Witten 115 from nursing homes.

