#### Data analysis

At T1, we will apply an analysis of covariance of the primary outcome physical function (SPPB scores). This outcome will be used to analyse the difference between the intervention and control group. In case of non-normally distributed data, we will apply a nonparametric covariance model [34]. The secondary outcomes will be evaluated with ANCOVAs, t-tests or distribution independent Mann-Whitney U-Tests. To compare the number of deaths, events leading to discontinuation of the intervention, falls requiring medical attention, and hospital treatments, we will either calculate a χ2-test, Fisher exact test for binary variables or conduct a log-rank-test. Since the number of falls or falling in general has shown to depend on fear of falling and the amount of physical activity, we will perform a mediator analysis to correctly identify the effect of our intervention on falling [35].

Furthermore, we will perform exploratory analyses (multifactorial ANCOVAs and in case of non-normally distributed data adjusted rank transform tests [36]) and dichotomise and evaluate whether the participants in the subgroups setting (community setting, nursing home), sex, rural/urban setting, frailty, and baseline SPPB score show different results in our primary outcome SPPB or in secondary outcomes. We will perform this analysis at T1 and T2.

The evaluation of the intervention will be performed as intention-to-treat (ITT). The ITT analysis will include all randomised participants irrespective of the actual performance of the intervention. In case a participant decides to withdraw consent, we will ask for a final evaluation.

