#### Missing data

If the T1 or T2 evaluation of a participant cannot be performed, the research assistant will decide whether an informative (death, admission) or non-informative event (e.g. moving to another municipality) has caused the evaluation to be missed. Information on reasons for missing the T1 or T2 evaluation will be obtained from participants’ families, general practitioners or nursing teams.

Depending on this categorisation, the following methods for analysis taking into account missing values will be used: 1) informative missing: not able to attend [examination] because of previous nursing home admission, hospital admission or death - tied worst rank score method will be assigned a SPPB Score = 0. For secondary outcomes, we will proceed in a similar fashion. In the analysis, we will apply the worst-rank score analysis [37]. It considers only the relative ordering of the values and applies the minimum variance linear or best linear estimator. For secondary outcomes, we will proceed in a similar fashion. 2) In case of non-informative missing (not able to attend because participant moved to another place without one of the conditions mentioned above), we will proceed with multiple imputation. In case of non-normally distributed data, we apply a nearest neighbour multiple imputation approach to estimate the proportion of each then categorised variable [38]. For secondary outcomes, we will proceed in a similar fashion.

We will also perform an additional per-protocol analysis, which will only include participants whose follow–up examination has taken place at the designated time (6 months after baseline or follow-up ± 2 weeks). Individuals of the intervention group participating in less than 25% of the scheduled walks will be excluded in the per-protocol analysis.

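### The primary analysis is an ANCOVA in SPPB points in one section and an ordering-only analysis in another, and the normality rule does not settle which decides

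*Protocol article*

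**What the plan says.** Four statements in the Protocol article bear on how the primary outcome is tested.

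- **Sample size.** The calculation is for an ANCOVA with baseline SPPB as covariate, a 1-point difference, SD 2.8 and a covariate R-square of 0.5: "The total sample of 206 participants achieves 95% power to detect differences among the means using an F test with a 5% significance level". The total is raised to 345 for an expected 40% loss, attributed mainly to death and hospital admission.
- **Data analysis.** "At T1, we will apply an analysis of covariance of the primary outcome physical function (SPPB scores"). The next step is conditional: "In case of non-normally distributed data, we will apply a nonparametric covariance model [34"].
- **Missing data, informative losses.** For nursing home admission, hospital admission or death, "tied worst rank score method will be assigned a SPPB Score = 0". The section continues: "In the analysis, we will apply the worst-rank score analysis [37]. It considers only the relative ordering of the values". No condition is attached, and neither model in the Data analysis section is mentioned.
- **Missing data, non-informative losses.** Multiple imputation is used, but under non-normality "we apply a nearest neighbour multiple imputation approach to estimate the proportion of each then categorised variable". That yields category proportions, whereas both an ANCOVA and a rank analysis need a score for each participant.

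The intention-to-treat analysis keeps all randomised participants, so those scored 0 are in the primary comparison.

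**The concern.** An ANCOVA in points and an analysis of ordering answer different questions. The first estimates a difference in mean SPPB and treats a death as a fall from the baseline score to 0. The second asks who did better and uses the 0 only to place the participant last. The clinically relevant 1 point, on which the trial is sized, is defined only for the first.

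This is not a rare case. The events scored 0 are those the plan expects to cause most of a 40% loss. The text does not say which analysis decides, or whether the normality check comes before or after the zeros are assigned. At stake are what the primary result estimates and whether the stated 95% power belongs to the test that will be run.

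**Working it through.** **1. The plan's own figure.** Inputs from the Sample size section: difference 1, SD 2.8, R-square 0.5, two-sided 5%, power 95%.

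- Residual variance: 2.8² × (1 − 0.5) = 3.92.
- Normal approximation: n = 2 × (1.960 + 1.645)² × 3.92 / 1² = 101.9, so 102 per group.
- Noncentral F with SD of means 0.50 and 103 per group: λ = 206 × 0.50² / 3.92 = 13.14, error df 203, power 95.03% (94.8% at 102 per group).
- Loss: 206 / 0.60 = 343.3, so 344; the plan's 345 × 0.60 = 207.

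The figures reproduce. The design scale is a mean difference in points, and the inflation treats lost participants as absent from the analysis, not as present with a score of 0.

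**2. What the zeros do to an analysis in points.** Let a share p in each arm be set to 0 at random, with mean μ = 6 (assumed; the plan gives none) and SD 2.8 before zeros.

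- Difference in means: (1 − p) × 1, which is 0.90 at 10% and 0.60 at 40%.
- Variance: (1 − p) × 7.84 + p(1 − p) × 36. At 10%: 7.056 + 3.24 = 10.296, SD 3.21. At 40%: 4.704 + 8.64 = 13.344, SD 3.65.
- R-square with baseline: (1 − p)² × 3.92 / variance. At 10%: 3.175 / 10.296 = 0.31. At 40%: 1.411 / 13.344 = 0.11.
- If loss differs between arms, each percentage point of difference alone moves the estimate by 6 × 0.01 = 0.06 points.

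**3. Simulation.** 172 per arm, 3,000 trials per row, SPPB rounded and limited to 0–12, true 1-point effect among those assessed, equal random zeros, no other missing data.

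| Zeros | Shapiro-Wilk rejects residual normality | Estimate, points | Power, ANCOVA | Power, rank ANCOVA |
|---|---|---|---|---|
| 0% | 5.1% | 0.97 | 99.5% | 99.2% |
| 10% | 100% | 0.87 | 83.5% | 88.0% |
| 20% | 100% | 0.77 | 59.3% | 63.6% |
| 30% | 100% | 0.68 | 43.4% | 42.0% |
| 40% | 100% | 0.59 | 30.8% | 25.3% |

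The simulated SDs (3.16 at 10%, 3.62 at 40%) and R-squares (0.30 and about 0.1) agree with step 2.

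The order of operations therefore decides the test. Checked before zeros, about 5% of trials would leave the ANCOVA; checked after, all would.

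**4. How often the choice matters.** In two further sets of 2,000 trials per cell (10%, 17%, 28% and 40% zeros), ANCOVA and rank ANCOVA gave different significance verdicts in about 4% to 7% of trials with a true effect. In the 3,000-trial runs without an effect and with 10% to 40% zeros, each kept its level: 5.1% to 5.7% for ANCOVA and 4.9% to 5.5% for rank ANCOVA. The Monte Carlo standard error is √(0.05 × 0.95 / 3,000) = 0.4 percentage points.

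**The case against.** The strongest reply is that the plan can be read as one coherent sequence: ANCOVA first, a nonparametric covariance model if the data are not normal, and tied worst ranks entered into that model. On this reading, with zeros present, the switch has only one outcome, and that outcome agrees with the ordering-only statement. This largely stands. It means the two models in the Data analysis section are not in conflict with each other. It does not remove the conflict between points and ordering, because the ANCOVA is still the named first analysis and the only basis of the sample size, and the ordering statement is unconditional.

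A reader might go further and infer the following, which the document does not support:

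- **An inflated type I error.** Taking the best of ANCOVA, rank ANCOVA and an unadjusted Mann-Whitney test gives about 7% to 8% with zeros present, and those three disagree in about 10% to 20% of trials with a true effect. But the Mann-Whitney test is named only for secondary outcomes, and the plan does not propose choosing among results. Following the stated rule with Shapiro-Wilk as an assumed criterion gave 4.8% to 6.2% in 2,000 trials per cell, close to nominal. The Blinding section also withholds the meaning of the group codes from the statistician, which hampers a favourable choice.
- **Two competing primary time points.** The abstract states: "Primary endpoint is the physical function measured by the Short Physical Performance Battery (SPPB) at baseline, after 6 and 12 months". It includes baseline, which cannot be an endpoint, so it reads as the measurement schedule. Sample size and Data analysis both fix T1. This is an editorial note only.
- **No result in points at all.** A rank-based primary test does not prevent a supportive difference in points.

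The normality criterion itself may sit in an analysis plan not shown, so its absence is not held against the article.

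**Conclusion.** The point holds in this form: the article sizes and names the primary analysis as a mean difference in SPPB points, then states that the analysis uses only ordering, with informative losses scored 0. The deciding analysis and effect measure conflict, and the normality switch does not reconcile them.

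The effect on the significance verdict is moderate, at about 4% to 7% of trials between the two covariance models. The effect on what is estimated is larger: a true 1 point among those assessed becomes about 0.9 at 10% zeros and 0.6 at 40%. The 95% power is established for neither analysis once zeros enter.

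The simulated figures rest on a mean SPPB of 6, equal losses in both arms unrelated to baseline, an effect only among those assessed, Shapiro-Wilk as the check, and the plan's SD and R-square without the baseline truncation that eligibility imposes. They show direction and range and do not forecast this trial's power. In particular, if the intervention itself changed death or admission, the results would differ.

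**What to change.** 1. Name one primary analysis at T1 and remove the normality trigger. One workable choice is a rank-based covariance analysis adjusted for baseline SPPB and setting (the stratification factor), with informative losses as tied worst ranks. Report the probability of a better outcome with a 95% confidence interval.
2. Name the ANCOVA in SPPB points among living participants as the supportive estimate, with multiple imputation of the SPPB score itself and not of categories.
3. Check the 95% power for the chosen analysis across a range of informative losses, with those participants kept in, and restate it.
4. As an editorial correction, word the abstract so that T1 is primary and T2 secondary.

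The cost is wording and a power check before unblinding, with no change to data collection. The downside is that the primary effect is no longer in SPPB points. The supportive ANCOVA supplies that scale, but it compares survivors and so is not a fully randomised comparison. If the sponsor prefers to keep ANCOVA in points as primary, the ordering-only statement must go and the handling of death and admission must be defined for that model.

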## Discussion

This current paper presents the study protocol of a randomised, controlled interventional superiority study: the POWER study. This project targets older people with inadequate activity levels. With this study, we will evaluate a volunteer-supported physical activity intervention and expect this intervention to improve the overall health status of the participants in a wide range of health-related outcomes.

This is a pragmatic study evaluating the effect of an intervention consisting of three components: 1) motivation by another person; 2) physical assistance; 3) psycho-social support (company). The control treatment does not address these mechanisms directly but aims to keep participants interested and motivated to comply with study procedures.

This study includes some limitations. Despite the fact that participants are recruited through a range of different settings, there is a possibility of selection bias, as participants have to be willing to complete the intervention. Participants who do not participate may be more isolated, less active and have more health issues than the participants included in the study. Furthermore, selective attrition due to death and geographical mobility of participants is possible. As mentioned above, blinding of participants and the research team is impossible to achieve.

We propose and evaluate a simple, personal non-educational intervention that is addressing the problem of physical activity in the group of already physically restricted older people with a lack of social support. In our opinion, it is well suited for a wide range of individuals with widely differing educational and/or socioeconomic backgrounds. In addition, participants with language barriers, who would be left out of many educational programmes, will be able to participate in the same way as other participants. The intervention provides a realistic way to motivate older people to become physically more active. Not relying on professional input, it requires limited financial or staff resources. The fact that the service will be provided personally by volunteers, will increase participants’ motivation and improve their quality of life.

## Data Availability

Not applicable.

## Abbreviations

BMBF: Federal Ministry of Education and Research
CDT: Clock-drawing-test
CFS: Clinical Frailty Scale
DLR: The German Aerospace Centre
FES-I: Falls Efficacy Scale
ICD: International Classification of Diseases
ITT: Intention-to-treat
KKS: Coordination Centre for Clinical Trials
MMSE: Mini-Mental-Status-Examination
SPPB: Short Physical Performance Battery
WHO: World Health Organization
